#### Primary Outcome

The primary outcome measure of the study will be time to return to normal activities (RNA). The Patient-Reported Outcomes Measurement Information System (PROMIS) Physical Functioning item bank version 1.2 will be used to measure limitations in daily activities. This item response theory (IRT)–based item bank has been developed and validated in the United States and translated into Dutch-Flemish [31,32]. Initial validation studies in Dutch patients confirmed the unidimensionality and underlying calibration of the IRT model (personal communication, article submitted). This item bank consists of 121 activities. We made a selection of the 29 most relevant activities for this study (Multimedia Appendix 2). We considered the 92 excluded activities as not being affected by the type of surgery (eg, “Can you brush your hair?”) or as duplicate activities. The list of 29 activities will be presented to the patients at baseline (prior to surgery), and they will be asked to select 8 activities which are most relevant for them in daily life. In this way, patients will design their own personal physical functioning short form. Since items in an IRT-based item bank are calibrated onto the same continuum, one can select any subset of questions in that bank and the scores obtained from the derived short forms are comparable to that from the complete bank [33]. In the follow-up questionnaires, patients will only receive those PROMIS questions regarding the 8 activities that they selected before surgery as relevant to their personal life. Items are scored on a 5-point scale with 1 as most limited and 5 as no limitation. In addition, they will be asked postoperatively whether they can perform this activity on the same level as before surgery. If they answer “yes,” they are asked to fill in since when (date), and the question will no longer be repeated in the following questionnaires. If the question is answered with a “no,” the question will be asked again at the next follow-up moment. For each patient, this will result in 8 dates of resumption of their activities. These dates will be converted into time periods by calculating the number of days that have elapsed between the date of surgery and the date of the resumption of that particular activity. The moment of resumption of the last activity on the list will be defined as the RNA moment and thus the primary outcome measure will be time elapsed between surgery and resumption of the last activity. If patients have not resumed 1 or more activities at 6 months, those activities will be censored. If information about the resumption of 2 or fewer activities is missing, the RNA moment will be calculated based on 6 activities. If information about the resumption of more than 2 activities is missing, the RNA moment cannot be calculated accurately and will be considered as missing data.

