
#### Secondary Outcomes

As secondary outcomes we will use the time until the first activity can be resumed and the moment that 75% of the activities are resumed. Scores of the physical functioning short forms will also be calculated by summarizing for each patient the scores of the 8 activities and transforming them into a T-score on the PROMIS physical functioning metric, where 50 represents the average score of the US population with an SD of 10. The following outcomes will also be measured:

Social participation: assessed with the PROMIS Ability to Participate in Social Roles and Activities version 2.0 short form 8a [34]Self-rated health: measured by the 3-level EuroQol-5D (EQ-5D-3L) [35]Durations of return to work (RTW) (only for the working population): the time until the first day on which work will be resumed and the time until full resumption of work activities will be assessedPhysical activity: assessed by the International Physical Activity Questionnaire (IPAQ) short form [36]Length of recovery: measured by the recovery specific quality of life questionnaire (RI-5) short form [37].Pain intensity: measured by the Von Korff questionnaire visual analog scale (VAS) [38].Patient satisfaction: measured with a self-developed patient satisfaction questionnaire focused on satisfaction with perioperative care, the care program (both groups), the website (both groups), the app (intervention group only), and the activity tracker (intervention group only).

**Table 2 table2:** Outcome measures, measurement instruments, and time points.

				Enrollment	Surgery	Post-allocation				
Time Point^a^				*T* _0_		*T* _1_	*T* _2_	*T* _3_	*T* _4_	*T* _5_

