### Data Collection

Data will be collected by means of self-reported electronic questionnaires at standard moments. Data will be collected in the month before surgery (T_0_) and 1 week (T_1_), 3 weeks (T_2_), 6 weeks (T_3_), 3 months (T_4_) and 6 months (T_5_) after surgery (Table 2). When data regarding RNA are missing during 2 measuring moments, an attempt will be made to collect the missing questions by telephone or email.

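### The primary outcome rule for missing activities can record a return to normal activities (RNA) in a patient last known not to have returned, and sets aside usable event-free follow-up

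*Protocol article*

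**What the plan says.** All of the rules are in the protocol article, mostly under Primary Outcome.

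- Definition: "The moment of resumption of the last activity on the list will be defined as the RNA moment".
- Collection: after a yes the patient gives a date, and "the question will no longer be repeated in the following questionnaires". Otherwise, "If the question is answered with a “no,” the question will be asked again at the next follow-up moment".
- Censoring, stated only for the end of follow-up: "If patients have not resumed 1 or more activities at 6 months, those activities will be censored".
- One or two activities missing: "If information about the resumption of 2 or fewer activities is missing, the RNA moment will be calculated based on 6 activities".
- More than two missing: "the RNA moment cannot be calculated accurately and will be considered as missing data".

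Three other sections bear on this. Data Collection provides a recontact: "When data regarding RNA are missing during 2 measuring moments, an attempt will be made to collect the missing questions by telephone or email". Effect Analyses names Kaplan-Meier and Cox methods for RNA. Economic Evaluation plans multiple imputation of missing cost and effect data. Secondary Outcomes separately lists "the moment that 75% of the activities are resumed", which for 8 activities is the sixth to be resumed.

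**The concern.** The repeat-until-yes design means that missingness in this outcome is tied to its value. When a patient stops answering, the fast activities already have dates, and the open ones were last answered no (or never answered). The rule does not separate this patient from one who did resume an activity but left the date blank.

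An invented example shows the effect. By the 6-week questionnaire a patient has dated 6 activities, the latest at day 35, and answers no for the other 2. No further contact follows. The rule records RNA at day 35, although the patient said at day 42 that 2 activities were not resumed. A patient who answers no for the same 2 activities at 6 months is censored.

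With 3 or more open activities, RNA becomes missing, although the patient is known to be event-free up to the last questionnaire. Kaplan-Meier and Cox methods use that information through censoring, and nothing in the article says that such patients enter the primary Cox analysis. If they do not, then among patients who stop responding the faster ones stay as events and the slower ones leave, even when dropout itself is random.

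At stake are the RNA curves and medians and, if dropout differs between arms, the HR.

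**Working it through.** **1. The plan's own figures.** For HR 1.4, two-sided 5% and 80% power:
- Schoenfeld: 4 × (1.960 + 0.842)² / (ln 1.4)², giving 278 events.
- Freedman: (1.960 + 0.842)² × (2.4/0.4)², giving 283 events.
- Both are within 3% of the stated 285.
- 285 / (0.975 × 0.95) = 307.7, rounded up to the stated 308.
- 308 × 0.975 × 0.95 = 285.3, so the plan already counts the 5% who drop out as giving no events.

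The point does not alter 285 or 308.

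**2. Direction.** RNA = max(T1, …, T8). For any subset S, the maximum over S cannot exceed the maximum over all 8. Using 6 activities therefore never delays RNA. If 2 are missing at random, the slowest is among them with probability 2/8 = 25%; if 1 is missing, 1/8 = 12.5%. If exactly the 2 slowest are missing, the value equals the 75% secondary outcome.

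**3. Size.** The article gives no activity-level data, so the following are assumptions:
- 8 lognormal activity times, log-SD 0.9, within-patient correlation 0.3, 0.6 or 0.8.
- About 2.5% of controls not returned by day 182; intervention times 0.80 of control times.
- Questionnaires at days 7, 21, 42, 91 and 182.
- Dropout unrelated to recovery, with the last completed questionnaire uniform over none, T1, T2, T3 and T4, and no recontact.
- 400,000 simulated patients per correlation. The full-data HR is 1.341, 1.289 and 1.275, not exactly 1.4.

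Control median RNA in days:

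| Correlation | Full data | Rule, 5% dropout | Rule, 10% | Rule, 20% |
|---|---|---|---|---|
| 0.3 | 46.2 | 45.6 | 45.0 | 43.7 |
| 0.6 | 38.7 | 38.3 | 37.8 | 36.9 |
| 0.8 | 34.6 | 34.3 | 33.9 | 33.2 |

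The shift is 0.3-0.6 day at 5%, 0.7-1.2 at 10% and 1.4-2.5 at 20%. Censoring at the last completed questionnaire gave the full-data control median to within 0.1 day throughout.

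**4. Patients affected at 5% dropout.**
- False events: 0.45-0.88% of patients, or 1.4-2.7 of 308.
- Set to missing: 2.56-2.62%, or 7.9-8.1 of 308.
- One fifth of dropouts (1% of patients, about 3 of 308) have no postoperative questionnaire and add nothing under either approach. So about 5 of the 8 have event-free follow-up that is lost.

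**5. HR.** With equal dropout of 5% the rule gives 1.339, 1.289 and 1.275, against 1.343, 1.291 and 1.277 under censoring. The largest gap at 20% is 1.339 against 1.350. With unequal dropout:

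| Correlation | 5% control, 15% intervention: rule vs censoring | 15% control, 5% intervention: rule vs censoring |
|---|---|---|
| 0.3 | 1.380 vs 1.345 (+2.6%) | 1.298 vs 1.344 (-3.4%) |
| 0.6 | 1.323 vs 1.293 (+2.3%) | 1.257 vs 1.294 (-2.9%) |
| 0.8 | 1.307 vs 1.279 (+2.2%) | 1.244 vs 1.278 (-2.7%) |

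The arm with more dropout looks faster than it is.

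**The case against.** The strongest reply is that the effect is negligible under the plan's own assumptions. At 5% dropout a handful of patients are affected, the median moves by less than a day and the HR hardly moves. The article gives no reason to expect 5% in one arm and 15% in the other. This stands, and it limits the size of the point. It does not make the rule right.

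Second, missing information need not mean dropout. A skipped item or a yes without a date is also missing, and those activities need not be the slowest. This stands too. The rule treats both kinds alike, though, and gives a wrong result for the first kind.

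Third, the telephone or email recontact can recover dates retrospectively, and the simulation leaves it out. It reduces the number of patients affected, but the rule for those who remain unreachable is unchanged.

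Fourth, the simulations make dropout random, which is the condition that favours last-contact censoring. That is a real limit of the fix.

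A reader might also infer more than the article supports:
- **A contradiction of intention-to-treat.** The article says RNA is considered missing. It does not say that the patient is removed from the Cox analysis, and a missing outcome is not in itself a departure from analysis as randomised.
- **Deletion from the cost-effectiveness ratio.** Economic Evaluation imputes missing effect data, and RNA is its effect measure.
- **RNA typically cut to 45% of its true value.** That is the mean of the sixth of 8 independent exponential times over the mean of the eighth (1.218/2.718), with exactly the 2 slowest missing. It is a worst case. With 2 missing at random the ratio is 2.45/2.718 = 90%.

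**Conclusion.** The rule is wrong as written for patients last known not to have resumed an activity. It can count them as returned, and its error runs in one direction only. For patients with more than 2 open activities it sets aside follow-up that the planned methods can use. Recontact and the imputation planned for the economic evaluation do not change this for the primary Cox analysis.

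The expected size is small at the planned dropout. It becomes material for the medians only with much more missing data, and for the HR only if missingness differs by arm. All sizes rest on assumed activity times and on dropout unrelated to recovery. The case for acting is that this is a stated derivation of the primary endpoint and that correcting it is cheap.

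**What to change.** Replace the two missing-data sentences under Primary Outcome with rules that separate an activity not resumed at last contact from one reported resumed without a date:

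1. Count an RNA event only when all 8 activities are reported resumed.
2. Otherwise censor at the last completed questionnaire or recontact at which a selected activity was known not to be resumed, however many are open.
3. For an activity reported resumed with a blank date, use the interval between the two questionnaires around the change, or imputation. The article states imputation only for the economic evaluation, so its use here would have to be added.
4. Use every known date. Read literally, the present wording uses 6 when 7 are known and does not say which is left out.
5. Keep the 6-activity version as a sensitivity analysis.

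The cost is wording and a few lines of derivation code, with no new data. The article states that data cleaning and analysis had not begun at submission, so at that stage the change could be made without knowledge of results. The event count falls slightly, by about 1-3 at 5% dropout, which the sample size already allows for. Last-contact censoring assumes that dropout is unrelated to recovery, and the plan should say so.

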
#### Secondary Outcomes

As secondary outcomes we will use the time until the first activity can be resumed and the moment that 75% of the activities are resumed. Scores of the physical functioning short forms will also be calculated by summarizing for each patient the scores of the 8 activities and transforming them into a T-score on the PROMIS physical functioning metric, where 50 represents the average score of the US population with an SD of 10. The following outcomes will also be measured:

Social participation: assessed with the PROMIS Ability to Participate in Social Roles and Activities version 2.0 short form 8a [34]Self-rated health: measured by the 3-level EuroQol-5D (EQ-5D-3L) [35]Durations of return to work (RTW) (only for the working population): the time until the first day on which work will be resumed and the time until full resumption of work activities will be assessedPhysical activity: assessed by the International Physical Activity Questionnaire (IPAQ) short form [36]Length of recovery: measured by the recovery specific quality of life questionnaire (RI-5) short form [37].Pain intensity: measured by the Von Korff questionnaire visual analog scale (VAS) [38].Patient satisfaction: measured with a self-developed patient satisfaction questionnaire focused on satisfaction with perioperative care, the care program (both groups), the website (both groups), the app (intervention group only), and the activity tracker (intervention group only).

**Table 2 table2:** Outcome measures, measurement instruments, and time points.

				Enrollment	Surgery	Post-allocation				
Time Point^a^				*T* _0_		*T* _1_	*T* _2_	*T* _3_	*T* _4_	*T* _5_
**Enrollment**										
		Eligibility screen		X					
		Informed consent		X					
		Allocation		X					
**Interventions**									
		**Intervention group**							
			Intervention part of the website	XXXXXXXXXXXXXXXXXXXXXXXXXXXXX						
			Mobile phone app	XXXXXXXXXXXXXXXXXXXXXXXXXXXXX						
			Activity tracker	XXXXXXXXXXXXXXXXXXXXXXXXXXXXX						
		**Control group**								
			Nonintervention part of the website	XXXXXXXXXXXXXXXXXXXXXXXXXXXXX							
**Assessments**										
	**Primary outcome measure**								
		Return to normal activities (PROMIS^b^ physical functioning item bank)		X		X	X	X	X	X
	**Secondary outcome measures**									
		Participation (PROMIS short form Social Roles)		X		X	X	X		X
		Self-rated health (EuroQol-5D-3L)		X			X	X	X	X
		Return to work (Return to work questionnaire)				X	X	X	X	X
		Physical activity (IPAQ^c^)		X			X	X	X	
		Recovery (RI-5^d^)		X		X	X	X		
		Pain intensity (VAS^e^)				X	X	X		
		Patient satisfaction (Satisfaction questionnaire)							X	

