		**Productivity loss**								
			Presenteeism: iPCQ^g^ and WHO-HPQ^h^	X		X	X	X	X	X
			Absenteeism: iPCQ	X		X	X	X	X	X
			Unpaid productivity: Cost questionnaire						X	X

^a^T_0_: 1 month before surgery; T_1_: 1 week after surgery; T_2_: 3 weeks after surgery; T_3_: 6 weeks after surgery; T_4_: 3 months after surgery; T_5_: 6 months after surgery.

^b^PROMIS: Patient-Reported Outcomes Measurement Information System.

^c^IPAQ: International Physical Activity Questionnaire.

^d^RI-5: recovery specific quality of life questionnaire short form.

^e^VAS: visual analog scale.

^f^Measured by the research team.

^g^iPCQ: Institute for Medical Technology Assessment (iMTA) Productivity Cost Questionnaire.

^h^WHO-HPQ: World Health Organization—Health and Work Performance Questionnaire.

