### Allocation

After inclusion, patients will be asked to complete the first online questionnaire (T_0_) within the month before surgery. After patients have completed the questionnaire, randomization will take place by means of a computer-based randomization list stratified regarding hospital, sex, and surgical procedure using permuted blocks, size 2. Patients are randomized to the intervention or the control group in a 1:1 ratio. The researcher performing randomization is independent from the recruitment or data analyses.

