### Data Analyses

#### Effect Analyses

All analyses will be performed in SPSS (IBM Corp). Baseline characteristics will be summarized using descriptive statistics and compared between the intervention and control group using *t* tests, Mann-Whitney U tests, chi-square tests, or Fisher exact tests. Survival analysis will be used to analyze time until RNA data. Both crude and adjusted analyses will be performed. Hospital, surgical procedure, and sex will be taken into account as covariates in the adjusted analyses because these are the factors for which stratification will apply. In addition, when there are clinically relevant differences between the intervention and the control group in the baseline characteristics or potential confounding factors, this will also be considered as a covariate in further analyses. To describe the distribution of the duration until RNA in both groups, the Kaplan-Meier method will be used. The Cox proportional hazard model will be applied to calculate HRs. Differences in secondary outcomes between the groups will be assessed by mixed models and multilevel logistic regression models for outcomes that are measured more than once during follow-up, and *t* tests, Mann-Whitney U tests, chi-square tests, or Fisher exact tests will be used when differences on 1 time point will be compared. Statistical analyses will be performed according to intention-to-treat principle, which will be compared to per-protocol analyses. Patients will be included in the per-protocol analyses when they used the intervention as intended, which will be defined as the generation of a convalescence plan on the website. This will be measured by a web log. Subgroup analyses will be performed regarding the surgical procedure (1. Cholecystectomy, 2. Hernia inguinal surgery and 3. Adnexal surgery) and type of surgery (gynecological vs surgical procedures). A post hoc analysis will be carried out on patients without major complications (definition described in Potential Confounding Factors).

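### Pain VAS, a repeated secondary outcome, has no preoperative value on the same scale, so its mixed model cannot condition on baseline VAS

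*Protocol article*

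**What the plan says.** The Secondary Outcomes section lists "Pain intensity: measured by the Von Korff questionnaire visual analog scale (VAS" among the secondary outcomes. Table 2 gives the timing: the row "Pain intensity (VAS^e" is marked at T1, T2 and T3 and is blank at T0. The footnote defines the time points from T0 onward as "1 month before surgery; T_1_: 1 week after surgery; T_2_: 3 weeks after surgery; T_3_: 6 weeks after surgery".

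Neighbouring rows do have a T0 mark, among them "Recovery (RI-5^d" and "Self-rated health (EuroQol-5D-3L". The Prognostic Factors section lists what else is taken before surgery: sociodemographic data, expectations about recovery and the PROMIS physical functioning T-score. It lists no pain score.

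The Allocation section places the T0 questionnaire ahead of allocation: "After patients have completed the questionnaire, randomization will take place by means of a computer-based randomization list". For the analysis, the Effect Analyses section states: "Differences in secondary outcomes between the groups will be assessed by mixed models", for outcomes measured more than once. It also says that clinically relevant baseline differences between the groups will be considered as covariates.

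**The concern.** Pain is measured three times after surgery and analysed longitudinally, yet it is the only repeated health or function scale in the schedule without a preoperative value. Burden does not obviously explain this, since an online T0 questionnaire already exists and is completed before anyone is allocated.

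Two parts of the analysis plan are affected. The mixed model for pain has no baseline VAS to condition on, so any variation between patients that a preoperative score would explain stays in the residual. And the rule that brings clinically relevant baseline differences into the model cannot see a difference in preoperative VAS pain. Stratified randomisation balances hospital, sex and procedure, but not variation in preoperative pain among patients within a stratum.

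**Working it through.** **1. Is the blank T0 cell real?** Reading Table 2 column by column:

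| Row | Marked at |
|---|---|
| PROMIS physical functioning | T0, T1 to T5 |
| Social participation | T0, T1, T2, T3, T5 |
| EQ-5D-3L | T0, T2 to T5 |
| IPAQ | T0, T2, T3, T4 |
| RI-5 | T0, T1, T2, T3 |
| Return to work | T1 to T5 |
| Pain VAS | T1, T2, T3 |

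Pain starts in the same column as return to work, which can have no preoperative value. The RI-5 row directly above pain carries a T0 mark. The gap is not a shifted column.

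**2. The plan's own figures.** The article states no standard deviation, correlation or power for pain. Its sample size concerns return to normal activities only. For HR 1.4, two-sided 5% and 80% power, the Freedman formula gives 283 events and the Schoenfeld formula 278, against 285 stated. Then 285 / (0.975 × 0.95) = 307.7, rounded up to 308 as stated. Nothing in this point changes those figures.

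**3. Precision forgone for pain.** Inputs: 308 patients and 5% dropout (Sample Size Calculation), so 308 × 0.95 / 2 = 146 per arm; two-sided 5% and 80% power; one time point. The correlation r between baseline and follow-up VAS is an assumption.

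- Residual variance after adjustment, relative to none: 1 − r²
- Equivalent sample size factor: 1 / (1 − r²)
- Detectable difference in SD units: (1.960 + 0.842) × √(2/146) × √(1 − r²) = 0.328 × √(1 − r²)

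| Assumed r | 1 − r² | Variance reduction | Sample size factor | Detectable difference (SD) |
|---|---|---|---|---|
| 0 (no baseline) | 1.00 | 0% | 1.00 | 0.328 |
| 0.1 | 0.99 | 1% | 1.01 | 0.326 |
| 0.2 | 0.96 | 4% | 1.04 | 0.321 |
| 0.3 | 0.91 | 9% | 1.10 | 0.313 |
| 0.5 | 0.75 | 25% | 1.33 | 0.284 |

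**4. The same loss seen as chance imbalance.** With 146 per arm, the difference in mean preoperative pain between arms has a standard error of √(2/146) = 0.117 SD. A fraction r of any such difference passes into follow-up: 0.3 × 0.117 = 0.035 SD at r = 0.3 and 0.5 × 0.117 = 0.059 SD at r = 0.5. This is another view of the loss in step 3 and should not be added to it.

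**The case against.** The planned analysis compares groups after surgery. It does not set out to analyse change in pain, or to separate surgical pain from pain carried over in an individual patient. Under randomisation stratified by hospital, sex and procedure, that comparison needs no baseline to be unbiased in expectation, and differences in preoperative pain between procedures are already balanced. This stands, and it limits the point to precision and chance imbalance.

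The size is also open. Surgery falls between T0 and T1 and is meant to treat the underlying condition, so low correlations are plausible. At r = 0.1 to 0.2 the gain is only 1 to 4%. The calculation takes one time point and no other covariates, so the gain beyond procedure and sex would be smaller. This stands too, which is why a range is shown.

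A reader might go further in three ways that the article does not support:

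- That pain cannot be adjusted for baseline at all. EQ-5D-3L, RI-5 and PROMIS physical functioning are all taken at T0, so cruder adjustment is possible; only the same-instrument baseline is missing.
- That the patients are known to be in pain before surgery. This is a plausible inference from the procedures, but the article does not say so. Its discussion says only that elective patients are in general not acutely ill or bedridden.
- That a needed predictor of the primary outcome has been lost. The article does not name pain as a prognostic factor for return to normal activities.

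The objection does not remove the facts that the omission is unexplained, is out of line with the other repeated scales, and has a partial remedy in data already scheduled.

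**Conclusion.** The point holds as a modest design weakness in one secondary outcome. No same-instrument preoperative pain score is scheduled, so the pain model may lose precision and cannot correct a chance imbalance in preoperative VAS pain. On assumed correlations of 0.1 to 0.5, the variance reduction forgone runs from 1% to 25%, and the detectable difference at one time point would fall from 0.328 SD to between 0.326 and 0.284 SD. The article gives nothing that narrows this range.

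It would be wrong to conclude that the pain comparison is biased. Randomisation protects it in expectation, and the primary outcome and the sample size of 308 are untouched.

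**What to change.** Before analysis, prespecify the T0 EQ-5D-3L pain/discomfort response as a baseline covariate in the mixed model for pain. It is scheduled for every patient before randomisation. The health states must be kept anyway to derive utilities, so no new data are needed. The article reports that data cleaning and analysis had not begun at submission.

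If any patients are still to be enrolled, add the same pain VAS to their T0 questionnaire. The article gives enrolment as starting in September 2015 and expected to end in August 2016, so few or none may remain.

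State as a limitation that a same-instrument baseline is missing for patients already enrolled.

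The costs are small but real. The EQ-5D-3L response has only three levels and is a coarse stand-in for a VAS, so it will recover only part of the possible gain. A VAS added during the trial exists only for later patients. The EQ-5D-3L response should therefore be the covariate for everyone, so that the adjustment does not depend on enrolment date.
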